**Discussion:**

We expect that RASP evaluation findings will demonstrate a minimum 10% reduction in high-cost health services utilization and corresponding 10% cost savings, and also a reduction in the wait times for patient consultations with psychiatrists to less than 30 calendar days, in both within-subject and between-subject comparisons. In addition, we anticipate that patients, healthcare providers and healthcare partners would express high levels of satisfaction with the new service.

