## Methods

### Study objectives

The primary objective of this study is to evaluate the effectiveness and impact of RASP on high-cost health services utilization (e.g. ED visits, mobile crisis visits and inpatient mental health utilization). To achieve this objective, we will conduct a within-subject comparison by analyzing health services utilization data from patients attending the RASP program one year pre- and post-assessment. Additionally, a between-subject comparison will be made using historical data from a control population consisting of patients referred by a PHP to see a mental health clinician before RASP implementation. Another primary objective is to assess qualitative data from healthcare partners' perceptions related to the impact of the RASP on access to community mental health care for patients and support for primary care providers, as well as to determine patient experiences and satisfaction with the program.

The secondary objectives of this study are to i) identify the sociodemographic characteristics of the population assisted by the RASP, ii) evaluate the prevalence and correlates of the various psychological conditions of the assisted population, iii) assess recovery, well-being, and risk measures in the assisted population at the program entry, and iv) compare health services utilization in the subset of patients who opt to participate in the Text4Support RCT with those who do not.

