The study seeks to address the following research questions:A.Effectiveness and Impact on Health Services Utilization of the RASP:Did RASP increase the volume of patients referred by PHP? Measured by the number of patients referred by a PHP for a psychiatrist consultation before and after RASP implementation.Did RASP increase the proportion of patients triaged by Central Intake services who had direct access to psychiatric consultations? Measured by the proportion of referrals received by central intake that were booked directly for psychiatry consultation, before and after RASP implementation.Did RASP reduce wait times for access to psychiatrists in the publicly funded MHAP? Measured by the number in calendar days waiting from date referral was received by Central Intake to date patient is scheduled for a psychiatric consultation before and after RASP implementation.Did RASP improve efficiency of the Community Mental Health Programs (CMHP) to address the mental health needs of patients with complex mental health needs? Measured by wait-times for assess to psychiatrists within the CMHP following a referral by a mental health clinician before and after RASP implementation.Did RASP reduce the volume of patients referred by PHP to the ED for a psychiatric consultation? Measured by the number of patients referred by a PHP for a psychiatrist consultation at the ED before and after RASP implementation.Did RASP reduce ED visits, mobile crisis visits, and inpatient mental health services utilization? Measured by the number of mental health and addictions (MHA)-specific ED visits, number of mobile crisis visits, number of MHA-specific hospital admissions, and number in calendar days in LOS for Central Zone patients, before and after RASP implementation.Did patients who attended the RASP and opted to participate in the Text4Support RCT differ in their health services utilization compared to patients who opted not to participate in the Text4Support RCT? Measured by the number of MHA-specific ED visits, number of mobile crises calls, number of MHA-specific hospital admissions, and LOS in calendar days, one-year post-RASP assessment.What are the costs and benefits to Nova Scotia Health from having a RASP for mental health? Measured by the net cost savings associated with RASP considering costs associated with the program and costs saved from avoided high-cost health services utilization (ED visits, mobile crisis visits, and inpatient treatments).B.Perspectives and Experiences of Healthcare Partners and PatientsWhat are healthcare partners' perceptions related to the impact of the RASP on access to community mental health care for patients and support for primary care providers? Measured by qualitative data from key informant interviews with program directors, psychiatrists, primary healthcare providers, MHA service leaders, and representatives from community organizations.What are the patients' perceptions related to their overall experience and satisfaction with the service received? Measured by quantitative and qualitative data from the RASP's satisfaction survey and qualitative data from focus group sessions with a sub-group of the assisted population.C.Population Characteristics and Mental Health MeasuresWhat proportion of patients seen at the RASP continued their treatment with PHP? Measured by the number of patients fully discharged back into the care of their primary healthcare provider with treatment recommendations (chart review data).What proportion of patients seen at the RASP were referred to a community mental health program? Measured by the number of patients referred to a community mental health program by RASP psychiatrists (chart review data).What proportion of patients seen at RASP needed additional psychiatric evaluation at the RASP? Measured by the number of re-referrals to RASP by a PHP.What are the sociodemographic characteristics of the assisted population at program entry? Measured by the frequency and percentages of the sociodemographic characteristics (e.g. age, sex of birth, gender, ethnicity, employment status, source of income, income range, relationship status, family support, housing status, education, provincial zone) (chart review data).What is the status of patients’ recovery and health quality index, and the prevalence of likely major depressive disorder (MDD), likely generalized anxiety disorder (GAD), low resilience, childhood trauma, substance use, and suicide risk at program entry? Measured by patient-completed validated scales scores (chart review data).What is the prevalence of patients' diagnoses made by RASP psychiatrists at program entry? Measured by the frequency and percentages of each psychiatry diagnosis after psychiatry assessment (chart review data).What are the risk factors for ED presentation for mental health concerns and inpatient psychiatric treatments? Measured by Odds Ratios using logistic regression models with sociodemographic and clinical data from the assisted population one year before and after RASP assessment date.

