
### Hypothesis

Based on the project Logic Model (Fig. 2), we anticipate that the RASP initiative will yield positive impacts in the short, medium, and long terms, leading to substantial changes in the capacity of mental health support and primary health care providers. Specifically, we hypothesize that RASP will result in a minimum 10% reduction in high-cost health services utilization (e.g. ED visits, mobile crisis visits, and inpatient treatments) and corresponding 10% cost savings. Additionally, we anticipate a reduction in the wait times for patient consultations with psychiatrists within the publicly funded MHAP to less than 30 calendar days. This forecast is expected to be found in both within-subject and between-subject comparisons. In addition, we hypothesize that at least 90% of patients attending the RASP will express satisfaction with the services received. Finally, we hypothesize that primary care providers and healthcare partners will express high satisfaction with RASP. These hypotheses are derived from anecdotal evidence gathered from a similar program implemented at Fort McMurray between 2013 and 2016 by the Senior Investigator.

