### Outcome measures

Primary outcome measures will include the mean differences in the frequency/duration/related costs of high-cost mental health services utilization (i.e., volume and proportion of mobile crisis visits, ED visits, hospital admissions and readmissions and associated LOS for each admission) between one year pre- and post-assessment date for same patients at RASP (within-subject comparison) and between the IG (RASP) and CG (historical data) (between-subjects comparison). Other primary outcome measures will be the mean difference in the number and proportion of total referrals booked directly for a psychiatrist and the number of calendar days for access to psychiatrists, also compared to the control group.

Secondary outcome measures include the mean difference in the frequency/duration/related costs of high-cost health services utilization one year post for patients who access the RASP and participate in the Text4Support RCT (to receive either daily supportive text messages or a single text message with a link to e-mental health resources) and patients accessing RASP but who do not participate in the Text4Support RCT. Other secondary outcome measures include a descriptive summary of the sociodemographic and clinical characteristics of the assisted population, the mean scores on the Patient Health Questionnaire 9 (PHQ-9) [38], Generalized Anxiety Disorder 7 (GAD-7) [39], World Health Organization 5 (WHO 5 Well-Being Index) [40], Brief Resilience Scale (BRS) [41], Recovery Assessment Scale (RAS) [42], Adverse Childhood Experience (ACE questionnaire) [43], Brief Substance use Craving Scale (BSCS) [44], and the Columbia-suicide severity rating scale (C-SSRS) [45], as well as the prevalence of likely MDD, GAD and low resilience. Patient overall impressions (i.e. barriers to accessing RASP, satisfaction level, likely recommend the service to others, etc.) and impressions on the experience (i.e. feelings of welcomeness, respect, enough time to talk, the problem addressed, and understanding of treatment) are part of the patient satisfaction quantitative evaluation. An in-depth evaluation of healthcare partner impressions and patient satisfaction will be obtained through qualitative key informant interviews until saturation is reached and no new themes and subthemes emerge.

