### Sample size considerations

With two staff psychiatrists and a clinical coordinator, we expect an average of six patients to receive comprehensive psychiatric assessments at the RASP each working day. Thus, we anticipate that the total number of patients accessing the service over the 24-month data collection period would be at least 2500. We also expect the sample size for the control population (patients whom a primary care provider referred to the MHAP Central Intake Services between May 2020 and May 2022) to be at least equal to the numbers seen at the RASP over a similar two-year time frame. Therefore, the data set to be generated from an overall sample of 5000 patients in this study would be large. With the assumption that the implementation of RASP will lead to at least a 10% reduction in high-cost health services utilization one-year post initial referral from a primary care provider for patients attending the service compared to patients who were offered a future appointment to see a mental health clinician as an entry point to the community mental health program, a power of 90% (β = 0.1) and a two-sided significance level of α = 0.05, and assuming an aggregated mean high cost health services utilization of 10 (SD =1) for the control population, we estimated that a sample size of 525 per group would be sufficient. Given that we expect at least 2500 patients per group in our study, it is highly probable that our study has more than sufficient power to detect the projected differences in high-intensity/cost health services utilization between the two groups.

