#### Health economic evaluation

We will conduct an economic evaluation through an effectiveness-implementation science lens. Specifically, we will conduct a cost-consequence analysis (CCA) from a Canadian single-payer perspective. The CCA will involve a disaggregated comparison of the costs and benefits (consequences) associated with RASP. The disaggregated analysis reports the intervention effects for the relevant primary and secondary outcomes in their natural units to aid value for money assessments. The study design, population, setting, and location are described elsewhere in this proposal.

We will compare outcomes (ED visits, crisis calls and inpatient days) and costs in the intervention group to the control group. Costing includes costs associated with the pre-implementation, implementation, and ongoing costs. These costs will include space and utilities, new hires specific to RASP, supplies, materials, and equipment, travel costs, volunteer time, and other in-kind donations. We will exclude all research-related costs. These cost data will come from the project documents. In addition, we will collect cost data on health resource use from the case costing centre in the Nova Scotia Health, supplemented with data from the literature if necessary.

Costing will also include costs saved from avoided ED visits, crisis response services and inpatient treatments. Cost analyses will use Nova Scotia Health 2023 costs to ensure relevance to decision-makers. We will estimate the intervention effect for the outcomes using appropriate treatment-effect econometric models with bootstrapping to quantify the uncertainty around the estimates. To enable cost comparisons, the cost of the current models of community-based mental health services, which involve waitlisting of all non-urgent patients (regardless of referral source and reason for referral) to see a mental health clinician as a gateway to receipt of community mental health services, including psychiatry, will be compared with the costs of alternative treatments offered expeditiously through RASP and primary care and community providers. We will compute the net cost savings associated with RASP. Our economic analysis will follow guidelines for economic evaluations, including using probabilistic sensitivity analysis to quantify the uncertainty around the implementation costs [48].

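### The primary wait-time outcome exists only for patients who obtained a psychiatric date, which selects differently in the two groups, and its forecast within-subject version is not defined.

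*Protocol article*

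**What the plan says.** The wait-time question under Study objectives gives this measure: "number in calendar days waiting from date referral was received by Central Intake to date patient is scheduled for a psychiatric consultation". It is to be compared between the periods preceding and following the programme's launch. Outcome measures lists among the other primary outcomes a mean difference in "the number of calendar days for access to psychiatrists, also compared to the control group". The Hypothesis section predicts "a reduction in the wait times for patient consultations with psychiatrists within the publicly funded MHAP to less than 30 calendar days" and adds: "This forecast is expected to be found in both within-subject and between-subject comparisons". The Abstract's Discussion ties this to wait time directly: "to less than 30 calendar days, in both within-subject and between-subject comparisons".

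Controls did not start with a psychiatrist. Study objectives describes them as "patients referred by a PHP to see a mental health clinician before RASP implementation". Sample size considerations calls them "patients who were offered a future appointment to see a mental health clinician as an entry point to the community mental health program". Health economic evaluation says that the earlier model put all non-urgent patients on a waitlist "to see a mental health clinician as a gateway to receipt of community mental health services, including psychiatry".

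Two neighbouring research questions matter here. One measures the share of Central Intake referrals given a direct psychiatric booking. The other measures waits for a psychiatrist inside the community programme after a clinician's referral. Both are compared before and after RASP.

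**The concern.** A mean of days waited can include only patients whose interval has an end date. If nearly everyone in one group has an end date and an unknown fraction of the other does, the difference in means mixes speed of access with who got access. Faster access is one of the programme's declared purposes and a named primary outcome, so a figure that cannot register failure to gain access is a weak basis for claiming success. Separately, the hypothesis promises a within-subject result for an outcome that appears to have only one value per patient.

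**Working it through.** The document gives no mean wait, standard deviation, booked share or sample size for wait time, so there is no wait-time figure to reproduce. Its one sample-size result, 525 per group, is for service utilization and does not bear on this point.

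**Step 1: who has a value in each group.**

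| | RASP group | Control group |
|---|---|---|
| How a patient enters | Attends RASP and consents (Study design; Participants and data collection) | Referred by a primary provider to Central Intake before RASP (Study design; Participants and data collection) |
| Index event | Psychiatric assessment (Study design) | Attendance with a community mental health clinician (Data analysis) |
| Psychiatric date needed to be in the group? | Yes | No |
| Has a wait value | All, by construction | Only those later booked with a psychiatrist |

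The document does not state in words that unbooked patients are dropped. That follows from an interval ending at a psychiatric date combined with a mean difference as the summary.

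**Step 2: does the companion measure supply the missing part?** It counts direct bookings among all referrals received. A control booked later, after seeing a clinician, has a wait value but is not a direct booking. The direct-booking share is therefore not the fraction of controls who contribute to the mean, and cannot be used to correct it.

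**Step 3: how insensitive the booked-only mean is (assumed inputs).** Let p be the share of controls booked within 365 days and M the mean wait among them. If every unbooked control is counted as waiting to day 365, the restricted mean over all referred is p × M + (1 − p) × 365. With M = 90:

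- p = 0.3: 27 + 255.5 = 282.5 days
- p = 0.5: 45 + 182.5 = 227.5 days
- p = 0.7: 63 + 109.5 = 172.5 days

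The booked-only mean is 90 days in all three cases.

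A second illustration assumes exponential control waits with latent mean m and a 365-day window. The booked share is 1 − exp(−365/m), and the restricted mean is m times that share.

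| m (days) | Booked by day 365 | Mean among booked | Restricted mean, all referred |
|---|---|---|---|
| 120 | 95% | 102 | 114 |
| 240 | 78% | 138 | 188 |
| 365 | 63% | 153 | 231 |
| 730 | 39% | 167 | 287 |

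The booked-only mean rises by 65 days (102 to 167) while the restricted mean rises by 173 (114 to 287). Both illustrations treat every unbooked control as still waiting, which is an extreme. They show insensitivity to non-access and do not estimate the bias in this study.

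**Step 4: the within-subject forecast.** Study objectives, Study design, and Participants and data collection define within-subject data as service utilization one year before and one year after the RASP assessment. Outcome measures places the within-subject comparison under utilization and compares wait days with the control group only. The wait belongs to the referral that leads to the psychiatric date, so a RASP patient has one index wait. An earlier wait could exist only for patients with a previous psychiatric referral, a subset the document does not define.

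**The case against.** The strongest reply is that the article states no rule for referrals without a psychiatric date, and that such a rule may sit in an analysis plan or supplementary table not shown here. That is fair as to silence. However, the article does fix the interval, the summary (a mean difference) and the comparator. A rule giving unbooked patients a value would change the stated outcome, not merely fill in a detail.

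Three stronger readings are tempting, and the document does not support them.

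- A reader might infer that the plan ignores patients who never gained access. It does not: the share booked directly has all Central Intake referrals as its denominator and is listed as primary alongside the wait. It answers the point in part.
- A reader might infer that RASP-era waits outside RASP are hidden. They are not simply hidden: one research question covers psychiatrist waits within the community programme before and after RASP, and the wait-time question itself refers to the whole publicly funded programme. What remains is that the primary comparison in Outcome measures is narrower, so its denominator is unsettled.
- A reader might infer that RASP's benefit will be understated. Losing slow or never-booked controls would push that way. But controls who passed the gateway may differ in case mix in either direction, and some unbooked controls may have had their needs met by a clinician. Counting those as waiting 365 days would inflate the control wait and favour RASP.

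On the within-subject forecast, it is fair to say that the operative definition in Outcome measures is already correct and that only the hypothesis wording is loose.

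**Conclusion.** The point holds in this form. As defined, the primary wait-time comparison sets a mean over all RASP attenders against a mean over only those controls who reached a psychiatric booking, and the direct-booking measure does not repair it. The conclusion rests on the outcome definition and on the described control pathway; the urgent or directly booked share among controls is not given. The direction and size of the bias cannot be determined from the document. The figures above rest on assumed booked shares and waits and show only that the planned mean can stay unchanged while access differs widely.

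The within-subject wait-time forecast cannot be tested as written. This is a contradiction between the hypothesis and the design, small in consequence because no within-subject wait analysis is specified. Neither part affects the utilization outcomes. Both should be changed before the wait-time data are analysed.

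**What to change.** 1. Define the analysis set as all primary-provider referrals received by Central Intake in each period, whether or not the patient was seen at RASP or by a psychiatrist.
2. Analyse time from referral to psychiatric consultation, with discharge or resolution at clinician level as a competing event and administrative censoring at 365 days or end of data. Simple censoring of clinician-resolved patients would treat them as still waiting and should be avoided.
3. Report the cumulative proportion seen by day 30, the plan's own threshold, and by day 365, for each period. Keep the booked-only mean as a descriptive supplement beside the share booked.
4. Remove wait time from the within-subject forecast in the Hypothesis section and the Abstract.

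The cost is wording plus a modest amount of standard analysis. The planned outcome already needs referral and booking dates; dates of clinician-level discharge or resolution would have to be extracted where recorded. De-identified dates for RASP-era referrals not seen at RASP may need a minor ethics note, because the existing consent and waiver arrangements are described for RASP patients and controls.

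### The prevalence of substance use is to be read from patient-completed scales, but the only substance-related scale listed is a craving scale

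*Protocol article*

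**What the plan says.** The research questions listed under Study objectives (part C) ask for the "prevalence of likely major depressive disorder (MDD), likely generalized anxiety disorder (GAD), low resilience, childhood trauma, substance use, and suicide risk at program entry". The source is named directly after the list of conditions: "low resilience, childhood trauma, substance use, and suicide risk at program entry? Measured by patient-completed validated scales scores (chart review data").

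The Outcome measures section then gives the secondary outcomes. It starts with "the mean scores on the Patient Health Questionnaire 9 (PHQ-9) [38"] and continues through eight scales, among them the "Adverse Childhood Experience (ACE questionnaire) [43"], the "Brief Substance use Craving Scale (BSCS) [44"] and the Columbia suicide severity scale. The sentence ends with a shorter list of prevalences: "as well as the prevalence of likely MDD, GAD and low resilience".

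Three other places bear on the point:

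- The section describing the program says that the psychiatrist's report on each patient covers, among other things, a history of drug and alcohol use.
- A separate question in part C plans frequencies and percentages of each diagnosis made by the program's psychiatrists.
- Participants and data collection says that scale results and diagnoses come from the initial screening forms, and that a supplementary table (S2, not shown) details variables and sources.

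**The concern.** A prevalence of use needs an instrument that separates those who use from those who do not. A craving score orders patients on something related but different. Someone who uses regularly may report little craving, and someone who is abstinent may report a lot. Whatever threshold is applied, the resulting proportion describes craving.

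The reported figure would be part of the description of whom the program reaches, and readers would take it as a rate of substance use. A further effect is possible but not stated in the plan. The protocol intends logistic regression for risk factors for emergency presentation and inpatient treatment, using sociodemographic and clinical data, and its Background names substance abuse as a predictor of recurrent emergency visits. If the craving score stood in for substance use in those models, its association with emergency use would usually be weakened.

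**Working it through.** **Matching the question to the outcomes.** The plan has no figure to reproduce here, so the main check sets the two sections side by side.

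| Condition asked for (Study objectives, part C) | Scale in Outcome measures | Listed there as a prevalence? |
|---|---|---|
| Likely major depression | PHQ-9 | Yes |
| Likely generalized anxiety | GAD-7 | Yes |
| Low resilience | Brief Resilience Scale | Yes |
| Childhood trauma | ACE questionnaire | No, mean score only |
| Suicide risk | C-SSRS | No, mean score only |
| Substance use | Brief Substance use Craving Scale | No, mean score only |

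Six prevalences are asked for and three are listed, so 6 − 3 = 3 are unmatched. The three are not alike. For childhood trauma and suicide risk the scale addresses the construct and is scored per patient, so a proportion can be formed. For substance use the named source, patient-completed scales, contains only a craving instrument.

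**Illustration of size.** None of these inputs is in the documents; all are assumed: true use p = 0.30; share of users classed positive on the craving scale Se = 0.50 to 0.70; share of non-users classed positive f = 0.05.

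Apparent prevalence = p·Se + (1 − p)·f

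- Se = 0.50: 0.30 × 0.50 + 0.70 × 0.05 = 0.150 + 0.035 = 18.5%
- Se = 0.70: 0.30 × 0.70 + 0.70 × 0.05 = 0.210 + 0.035 = 24.5%

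The direction is not fixed. The scale would overstate use once f exceeds p(1 − Se)/(1 − p), which is 0.30 × 0.30/0.70 = 0.129 at Se = 0.70 and 0.30 × 0.50/0.70 = 0.214 at Se = 0.50.

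**Illustration for a risk-factor model**, only if the craving score were used there as substance use. Further assumptions: 10% emergency use in non-users, a true odds ratio of 3, and misclassification unrelated to the outcome. Odds in users = 3 × 0.10/0.90 = 0.333, so their risk is 0.25.

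- Se = 0.70: risk in positives = (0.21 × 0.25 + 0.035 × 0.10)/0.245 = 0.0560/0.245 = 0.229; risk in negatives = (0.09 × 0.25 + 0.665 × 0.10)/0.755 = 0.0890/0.755 = 0.118. Odds ratio = (0.0560/0.1890)/(0.0890/0.6660) = 0.2963/0.1336 = 2.22.
- Se = 0.50: risk in positives = (0.15 × 0.25 + 0.035 × 0.10)/0.185 = 0.0410/0.185 = 0.222; risk in negatives = (0.15 × 0.25 + 0.665 × 0.10)/0.815 = 0.1040/0.815 = 0.128. Odds ratio = (0.0410/0.1440)/(0.1040/0.7110) = 0.2847/0.1463 = 1.95.

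On these inputs a true odds ratio of 3 would appear as about 1.9 to 2.2.

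**The case against.** A reader might infer that all three unmatched prevalences cannot be answered. The documents do not support that. The research question itself states the prevalence aim, the ACE questionnaire and C-SSRS are collected for each patient, and for depression, anxiety and resilience the plan gives both a mean and a prevalence. Naming a mean therefore does not exclude a proportion. Missing cut-offs are no finding either: an article commonly leaves them to the fuller plan, and none is given for the three conditions that are listed.

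It is also fair to say that neither the items nor the scoring of the craving scale are in the article, that the supplementary variable table is not shown, and that substance-use diagnoses will be tabulated in any case. These points limit how firmly one can say which patients would be misclassified, and they show that the question can be answered from the chart. They do not repair the stated pairing. The question names patient-completed scales, the list offers only a craving scale, and no later cut-off turns craving into use.

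The regression consequence is conditional. The plan does not name the craving scale as a predictor, and the clinical data it mentions could include the diagnoses. A reader should not take the attenuated odds ratio as something the plan will produce.

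**Conclusion.** The point holds for substance use: the named source does not yield a prevalence of use. For childhood trauma and suicide risk there is only a small inconsistency between the research question and the outcome list.

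The conclusion assumes that the scale measures what its name says, and that the unseen supplementary table names no other patient-completed measure of use. If it does name one, Outcome measures should list it. The numerical ranges are illustrations on assumed inputs and carry no weight beyond showing that the gap could matter.

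The matter is secondary and descriptive. It leaves the primary comparisons of service use and the sample size untouched.

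**What to change.** 1. Report the Brief Substance use Craving Scale as craving, under that name.
2. Take the prevalence of substance use from the drug and alcohol history in the psychiatric report, with a stated definition of use and time window. Report substance-use diagnoses separately as diagnoses, since a diagnosis and use are different things. Alternatively, keep the scale as the source and reword the research question to craving.
3. If substance use is a predictor in the risk-factor models, use the chart-based variable there.
4. For consistency, add the prevalence of childhood trauma and suicide risk to Outcome measures. The mean scores can stay.

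Rewording and relabelling cost nothing beyond the edit. Using the drug and alcohol history means some extra abstraction, because it sits in the psychiatrist's report, whereas the scales and diagnoses come from the screening forms. The plan expects at least 2,500 program patients, of whom only those who consent are included, so the extra work is real. If it is too much, rewording the question is the cheaper route, with substance-use diagnoses still available from the planned tabulation.
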